#### Qualitative Interview Outcomes

Qualitative methodology allows participants to discuss their lived experiences and can account for specific details that quantitative methods may not be able to attain. The research team will conduct semistructured interviews using the focus group methodology. In addition, a subsample of these participants will conduct individual interviews with a member of the research team. Research questions will address the factors that contribute to substance use in Paterson. Semistructured individual interviews will be conducted after focus groups to clarify themes and explore deep issues in greater depth. The target sample size for the focus groups will be 100 youths. A subsample of youths (N=50) will be asked to participate in individual interviews following the focus group interviews. The interview guide will consist of questions pertaining to substance use perception and knowledge, mental health status, and needed neighborhood resources. This component of the study focuses on 3 specific research questions: (1) what are the social and environmental contexts of substance use initiation; (2) how do youths define mental health symptoms such as anxiety and depressive symptoms; and (3) what resources do youth in Paterson identify to be beneficial in reducing or preventing substance use?

#### Qualitative Data Collection

First, participants will be asked to complete a 60- to 90-minute focus group with a trained facilitator. Focus group methodology provides insight and understanding of the phenomena by allowing the researcher to examine interactions among participants [60]. Focus groups will be stratified by age (eg, 12-13, 14-15, 16-18, and 19-21 years), gender (eg, male, female, and transgender), and race (eg, Black, Hispanic, and Bangladeshi). We hypothesize significant differences in risk and protective factors for substance abuse and mental health by group. Each focus group will comprise 5-8 youth participants. Although previous research indicated that 3 focus groups can yield saturation [61], we anticipate conducting 12 focus groups to improve study rigor and account for saturation within each subgroup of youth. For each focus group, 2 facilitators will be involved. Facilitators will be closely matched to youth participants by race, ethnicity, and gender. Following the focus groups, a subsample of (N=50) youth will be asked to participate in individual interviews to triangulate the data and delve deeper into sensitive themes that arose in focus groups. The lead facilitator will also interview the participants individually. The second cofacilitator will take notes of observations of nonverbal exchanges, including displays of emotion and nervous gestures that took place during the interviews. Adaptive questions will be used to further understand the unique experiences that youths are sharing. All interviews will be recorded and transcribed. As the interview process develops, questions may be tailored based on the youths’ feedback. The youth and community advisory board will review, revise, and approve the focus group and individual interview questions. Participants will receive US $25 at the end of the focus group interview and US $25 at the end of individual interviews.

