### Participant Recruitment and Sample Size

The eligibility criteria for study participation included youth who were (1) aged between 13 and 21 years, (2) able to speak and read in English, and (3) reside in Paterson, New Jersey. We acknowledge that Paterson is a very diverse city with residents who speak several languages besides English. The study intends to take into account differences that will arise in age, race, socioeconomic status, and gender and will work with the community to develop appropriate interventions informed by findings to be most effective in preventing substance use and improving mental health outcomes of youth [49].

The study will use a convergent [50], mixed methods design involving multiple data collection components and the analysis of a ministrative data source, designed with the strengths of complex interventions framework in mind. Venue-based sampling [51,52], purposive sampling [53,54], and snowball sampling [55] will be the 2 primary sources of recruitment for participants. The youth and community advisory board will be used as key informants to identify places where youth often congregate when they are not in school. Studies that focus on youth and use venue-based sampling have demonstrated that they can tap into at-risk groups and provide important information about environments and hard-to-reach populations to better inform interventions. Purposive sampling will involve recruiting youth through partnering youth-serving organizations and schools that have direct access to youth in the specified age range by using venue-based sampling.

Purposive sampling [53,54], also referred to as *judgmental* or *expert sampling*, is a type of nonprobability sample. The main objective of a purposive sample is to produce a sample that can be logically assumed to be representative of the population. This is often accomplished by applying expert knowledge of the population to select a sample of elements that represents a cross-section of the population in a nonrandom manner. The youth and community advisory board will assist in recruiting eligible participants by passing out flyers and emailing listservs.

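### Twelve focus groups of 5-8 youths give 60-96 participants, not the target of 100; the subgroup saturation claim can hold only one factor at a time; and the example youngest age band conflicts with eligibility

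*Protocol article*

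**What the plan says.** All the relevant text is in the Methods of the protocol article.

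- **Target.** Qualitative Interview Outcomes: "The target sample size for the focus groups will be 100 youths". A subsample of 50 is then to be interviewed individually.
- **Number and size of groups.** Qualitative Data Collection: "Each focus group will comprise 5-8 youth participants", and "we anticipate conducting 12 focus groups to improve study rigor and account for saturation within each subgroup of youth".
- **Benchmark.** The same sentence opens with "Although previous research indicated that 3 focus groups can yield saturation", citing an outside source.
- **Strata.** "Focus groups will be stratified by age (eg, 12-13, 14-15, 16-18, and 19-21 years"), together with "gender (eg, male, female, and transgender") and "race (eg, Black, Hispanic, and Bangladeshi"). Each list is introduced as an example. The text does not say whether the three factors are crossed or taken one at a time.
- **Eligibility.** Participant Recruitment and Sample Size admits youth "aged between 13 and 21 years". The Abstract and the Objectives section give the same range.

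**The concern.** Three statements do not fit together: the target against the number and size of groups, the saturation claim against the number of possible subgroups, and the youngest age band against the eligibility criterion.

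The first matters because a stated sample size should be one that the stated design can deliver.

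The second matters because the protocol expects risk and protective factors to differ between groups, and its Discussion plans to adapt the intervention to gender, race and developmental stage. If saturation is claimed for subgroups that no focus group covered, that claim passes into the choice and adaptation of the intervention.

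The third matters because a waiver of parental consent is to be sought for minors and the groups discuss sensitive topics. The lowest age admitted should therefore read the same everywhere.

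**Working it through.** **Inputs.** Target 100 (Qualitative Interview Outcomes). From Qualitative Data Collection: 12 groups, 5-8 youths per group, 3 groups cited as able to give saturation, and example levels of 4 ages, 3 genders and 3 races. Eligible age 13-21 (Participant Recruitment and Sample Size).

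**1. Can the plan's figure of 100 be reproduced?** Participants = groups x youths per group.

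- Smallest: 12 x 5 = 60.
- Largest: 12 x 8 = 96.
- Shortfall against 100: 100 minus 96 = 4, up to 100 minus 60 = 40.
- Mean group size needed: 100 ÷ 12 = 8.33, above the stated maximum of 8.
- Groups needed for 100: 100 ÷ 8 = 12.5, so at least 13 if groups are nearly full; 100 ÷ 5 = 20 if all are at the minimum.

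The figure of 100 is not reproduced by any group size within the stated range.

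**2. Saturation, one factor at a time.** Here each group counts once towards an age band, once towards a gender and once towards a race.

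| Factor | Example levels | Groups per level if balanced | Youths per level |
|---|---|---|---|
| Age | 4 | 12 ÷ 4 = 3 | 15 to 24 |
| Gender | 3 | 12 ÷ 3 = 4 | 20 to 32 |
| Race | 3 | 12 ÷ 3 = 4 | 20 to 32 |

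Every level reaches 3. Such an allocation exists: one group in each of the 4 x 3 = 12 age-by-gender combinations, with race rotated so that each race has 4 groups. Age has no slack, because 4 bands x 3 groups = 12 uses every group. Gender and race need 3 x 3 = 9 each and so have 3 to spare.

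**3. Saturation, factors crossed.**

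- Cells: 4 x 3 x 3 = 36.
- Cells with no group, at best: 36 minus 12 = 24.
- Average groups per cell: 12 ÷ 36 = 0.33.
- Groups needed if 3 were required in every cell: 36 x 3 = 108.

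Crossing only two factors does not meet the benchmark either. Age by gender, or age by race, has 12 cells and so 1 group each. Gender by race has 9 cells and would need 9 x 3 = 27 groups.

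**4. Age band.** The example youngest band runs from 12 to 13; eligibility runs from 13 to 21. One of the two ages in that band is ineligible.

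**The case against.** The strongest reply concerns saturation. A reader might infer that 12 groups can serve at most 4 strata, that most subgroups will have one group or none, and that 108 groups would be needed. The documents do not support that as a flat statement. The levels are only examples, crossing is never stated, and taken one factor at a time 12 balanced groups meet the benchmark at every level. The benchmark is also softer than a rule: the text says that 3 groups can give saturation, not that 3 are required in every cell. The 50 individual interviews are meant to deepen the same material. All of this stands, and it limits the saturation point to its conditional form.

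On the other side, some of the text leans towards groups that are alike on several factors at once. Facilitators are to be matched on race, ethnicity and gender, and Qualitative Data Analysis refers to groups whose members are similar. The one-factor reading also needs a balanced allocation, for example 4 transgender and 4 Bangladeshi groups, and this is not stated. The ambiguity is therefore real, but it does not show that the claim fails.

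On the target, one can reply that 12 is anticipated, 100 is a target, and one more group could close the gap. That is fair as to size: the shortfall of 40 arises only if every group runs at 5. The text still gives three figures that cannot all hold. The share of participants who would be interviewed (50 of 60-96, or 52-83%) is not a further fault, because the protocol fixes no proportion.

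On age, a reader might infer that 12-year-olds will be enrolled. Nothing shows that. The band is an example and the 13-21 range appears in three places, so this is a wording conflict.

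A reader might also conclude that the groups should be stratified on a single factor. That would give up the gender and race stratification that the protocol intends, and the figures do not require it.

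**Conclusion.** The point holds in three limited parts.

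- **Target.** The stated 100 cannot be reached with 12 groups of 5-8, which give 60-96. This needs no assumption beyond each place in a group being filled once; a youth attending two groups would only lower the count.
- **Saturation.** The claim can meet the protocol's own benchmark if subgroups are single-factor levels, the groups are allocated evenly, and each group is homogeneous on each factor. If the factors are crossed, at least 24 of up to 36 cells have no group. This part rests on the example levels being the ones used; other levels would change the counts.
- **Age band.** The example band of 12-13 contradicts the eligibility range.

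The effect is confined to the qualitative component. The survey target of 720 and the structural equation modelling are untouched. The corrections are worth making because they are cheap and because subgroup findings are meant to guide the intervention.

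**What to change.** 1. Restate the focus-group target as 60-96 youths for 12 groups of 5-8. Keeping 100 would instead mean planning at least 13 groups, with the added field work.
2. State that the saturation claim applies to the levels of each factor taken singly, and set out an allocation of the 12 groups that gives every level at least 3. Make no saturation claim for age-by-gender-by-race combinations. Because age has no slack, say what happens if a planned group cannot be held.
3. Reconcile the youngest age band with the eligibility criterion, so that one lower age limit applies throughout.

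The cost is protocol wording and an allocation table, with no added groups. The downside is a slightly smaller stated sample and a weaker claim about intersectional subgroups.

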#### Quantitative Data Collection

For each venue identified, the informants (members from the youth and community advisory board) will provide the name, address, type of venue, and preferred time. Youth and Community Advisory Board members and research staff will visit the venues identified. Parental consent will be requested to be waived because of confidentiality and sensitivity of the study for youth aged <18 years [60]. On agreeing to the study, participants will be asked to complete a brief 15- to 20-minute open survey onsite (eg, using an iPad or paper format version). Participants will also have the opportunity to schedule to complete the survey at a community-based partnering organization and schedule to be a part of the focus group. We will recruit at least 720 youths through venue-based sampling at venues and purposive sampling through community partners (eg, schools and youth-serving organizations) to complete surveys within the first 2 years of the project. The youth will be provided with the survey via a web-based platform. Youth will provide their responses to the survey questions in a secure location. They will be honest with their responses and will have the ability to change or alter previous responses. Surveys will be administered via Qualtrics, a secure survey tool, through the principal investigator’s university license. Questions in Qualtrics will be presented in a randomized format for each participant. Responses will be automatically populated in Qualtrics. The principal investigator will have sole access to the Qualtrics account and will download all the data once we have reached the intended number of participants for the study. Deidentified response data will be stored using a unique code representing each participant. Data will be stored confidentially via the secure databases of principal investigators’ institutions (eg, SPSS [IBM Corporation]). The attribution rate in the study will be operationalized as the number of participants who complete the consent to participate but did not complete the full study. Complete data will be used for the research analysis.

### Measures

#### Tobacco, Drug, and Alcohol Use

We will measure past 30-day drug use and lifetime drug use using items from the Centers for Disease Control and Prevention Youth Risk Behavior Survey [62]. The following drugs will be measured: alcohol, marijuana, tobacco, e-cigarettes or vape pens, hookah, opioids, and marijuana. An example of an item is “How many times did you use marijuana or hashish in the last 30 days?” Participants respond to these items on a 7-point scale (1=0 days; 2=1-2 days; 3=3-5 days; 4=6-9 days; 5=10-19 days; 6=20-29 days; and 7=all 30 days).

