## Introduction

### Background

Youth substance use continues to be a major public health issue in the United States, as it has reached epidemic proportions [1-3]. According to the National Institute on Drug Abuse and for the purposes of the current proposal, substance use is defined as the use, misuse, and abuse of substance—both licit and illicit drugs and alcohol. In a national sample assessing drug use among adolescents and teens, approximately two-thirds of students reported they had tried alcohol by the 12th grade, followed by marijuana (45%) and cigarette use (31%) [4]. Furthermore, youth who use substances are at risk of both acute (eg, changes in appetite, wakefulness, heart rate, and blood pressure) and long-term (eg, heart or lung disease, cancer, mental illness, HIV/AIDS, and hepatitis) consequences on their health [5]. Of importance, youth growing up in low-income urban areas are particularly vulnerable to substance use as well as their negative health consequences [6-8]. Given the long-term consequences of early substance use, it is important to identify factors that increase youth vulnerability to drug use, as they may be important targets for future interventions [8]. Urban youth may be exposed to traumatic conditions on a daily basis that affect their mental health, leading them to use poor coping mechanisms such as sexual risk taking and substance use [9,10]. Although interventions exist to tackle this complex issue, these interventions show limited effectiveness and only serve a subsample of youth substance users, given that much of the sampling and dissemination occurs within school contexts. Often neglected in the receipt of these services are youth who are truant or not engaged in school-based services [11-15]. Sampling bias is a consequence of using methods that do not provide all members of the population of interest equal probability of being sampled [13]. This type of error is common in youth substance use surveys, where youth who are engaging in higher levels of substance use are less likely to be sampled and less likely to complete these surveys [14,15]. Nonetheless, the likelihood of falling into a potential sample frame may in some cases be associated with substance use behaviors [13-15]. Therefore, substance use research may be uniquely vulnerable to sample coverage error. Youth who do not attend school on a regular basis or who have dropped out may be more likely to have increased substance use [16,17] and may be particularly vulnerable to the negative effects of substance use. Thus, the systematic exclusion of this population underestimates prevalence estimates of substance use among youth, which can, in turn, affect policy, funding decisions, and the development and generalizability of prevention and intervention efforts. Effective interventions are informed by demographic, contextual, and vulnerability factors as well as the unique experiences and perspectives of individuals in the target population. It is vital for substance use researchers to develop strategies for reducing sampling errors to include a wider representation of youth within a community. Using innovative methods, such as venue-based sampling, to reach the most vulnerable youth, this study aims to understand the effects of neighborhoods on youth substance use and mental health.

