### Objectives

This study aims to use community-based and innovative methods, such as venue-based sampling and CBPR, to gain a better understanding of the prevalence of substance use and important correlates among youth aged between 13 and 21 years within a lower-income, urban community. Historically, research in this area has focused on individual- and family-level factors that influence youths’ substance use patterns [36]. This protocol will describe the goal of the research; the intended population; and the methods that will be used for sampling, recruitment, and analyses. Specifically, this study will use venue-based sampling and CBPR as a recruitment method to identify vulnerable youth. Specifically, we hope to (1) identify the prevalence of substance use among youth; (2) understand important antecedents and correlates of substance use at the microsystem, exosystem, and macrosystem levels; and (3) use this information to inform social, environmental, and culturally appropriate interventions to address substance use and its correlates among youths in a lower-resourced urban community.

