### Youth Substance Use and Mental Health Trends in Paterson, New Jersey

Local-level data collected by a coalition in Paterson, New Jersey, found that 1 in 4 youth in Paterson used marijuana in the past 30 days [39], indicating that marijuana is the most widely used substance among the youths, followed by alcohol. Compared with other residents in Passaic County, Paterson residents have higher access to alcohol because of the high number of alcohol outlets in the city [39]. Thus, Paterson is a unique city to investigate and uses venue-based sampling techniques for this study because of the following reasons: (1) significant representation of the 2 largest ethnic groups in the nation (Black and Hispanic) that reside in Paterson and (2) the city’s wide availability of licit and illicit drugs that may impact community norms and values. For example, based on the parameters set by the New Jersey Division of Alcoholic Beverage Control [40], the city of Paterson with more than 147,000 residents should not exceed a total of 49 consumption licenses, including restaurants and bars, and 19 off-premises licenses, including liquor stores and bodegas. However, Paterson is only 8.4 square miles and has more than 200 alcohol outlets—4 times the legal limit because of grandfather clauses [37]. Alcohol outlet density is not only associated with increased crime, violence, and heavy alcohol and drug use but also provides Paterson youth with greater access to alcohol, leading to an increased probability of underage drinking [41-43]. Among Paterson youth aged between 13 and 18 years, 30% of youth reported that they had used alcohol before the age of 13 years [39]. Local-level data show that Paterson youth who drank alcohol during the past 30 days were also 3 times more likely to smoke marijuana before the age of 14 years [39]. Of note, 60% of Paterson youth reported purchasing alcohol from liquor stores and 40% of Paterson youth admitted to having an adult purchase alcohol from liquor stores for them [39]. Furthermore, Black (33.3%) and Hispanic (29.7%) Paterson youth reported the highest marijuana use before the age of 13 years [39]. In addition, the city is currently facing an extreme opioid crisis, with Paterson being ranked the second city in New Jersey for the highest rate of heroin abuse [44]. Among Paterson youth, 6.2% reported using cocaine and 6.8% reported using heroin; these rates are higher than the state averages [39]. These findings highlight the need to address substance use among Paterson youth, specifically, investigating antecedents and correlates to inform interventions to reduce substance use among youth. Although empirical studies suggest a bidirectional relationship between substance use and mental health [41], it is important to acknowledge that they are correlated and may influence each other, leading to poorer short- and long-term outcomes. Indeed, among Paterson youth sampled, there is a high mental health burden, as 50% of youth reported experiencing depressive symptoms and 57% reported experiencing anxiety symptoms [39]. Overall, 70% of youth who used either alcohol or marijuana in the past 30 days reported experiencing greater symptoms of anxiety and depression [39]. Given that both depression or anxiety symptoms and substance use are correlated and are associated with other negative health outcomes [45,46], it is important to understand these associations to inform and improve interventions aimed at decreasing mental health disparities and limiting substance use.

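### The list of measured drugs names marijuana twice and omits cocaine, which the protocol itself reports as used by 6.2% of Paterson youth; it also leaves unclear whether heroin can be reported apart from other opioids

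*Protocol article*

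**What the plan says.** The first aim, under Objectives, is to "identify the prevalence of substance use among youth". The Background section sets the scope of that term for this proposal: "substance use is defined as the use, misuse, and abuse of substance—both licit and illicit drugs and alcohol".

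The section on local substance use and mental health trends then makes the case for working in this city. It states: "Among Paterson youth, 6.2% reported using cocaine and 6.8% reported using heroin; these rates are higher than the state averages". It also describes "Paterson being ranked the second city in New Jersey for the highest rate of heroin abuse". It goes straight on to say that such findings show the need to address substance use in this population.

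The measurement section, Tobacco, Drug, and Alcohol Use, gives the source of the questions and the recall windows: "We will measure past 30-day drug use and lifetime drug use using items from the Centers for Disease Control and Prevention Youth Risk Behavior Survey". Its next sentence fixes the content: "The following drugs will be measured: alcohol, marijuana, tobacco, e-cigarettes or vape pens, hookah, opioids, and marijuana". No other section adds a drug to the survey. Under Quantitative Data Collection the target is at least 720 youths, each completing one survey of 15 to 20 minutes.

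**The concern.** The measured list and the stated purpose do not match. A drug that the protocol uses to justify the study is missing from the survey meant to measure prevalence, while another drug is listed twice. The repeat is a sign that the list was not checked before printing.

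What is at stake is the first aim. A drug that is not asked about cannot be recovered in analysis. The planned likelihood-based handling of missing data deals with unanswered questions, not with questions never put. The Background argues that earlier surveys understate prevalence because they miss certain youth. Leaving out a drug pulls an overall prevalence figure in the same direction. According to the Discussion, the findings also inform the choice and adaptation of the prevention intervention, so a gap in the survey carries forward.

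For heroin the problem is one of clarity. It belongs to a listed category, but a reader cannot tell whether the survey will give a heroin figure to set beside the local rate.

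**Working it through.** The protocol states no figure that depends on this list, so there is nothing to reproduce. The check is a comparison of texts, followed by arithmetic for scale.

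**1. Count the list.** The entries are alcohol, marijuana, tobacco, e-cigarettes or vape pens, hookah, opioids and marijuana. That is 7 entries and 7 − 1 = 6 distinct ones.

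**2. Is the list closed?** It is introduced as the drugs that will be measured, with no marker that it gives examples only. Elsewhere (for instance in Qualitative Data Collection and Quantitative Data Collection) the article marks illustrative lists with eg. The reference to the Youth Risk Behavior Survey names the source of the items. The sentence after it says which drugs are covered, so the reference does not bring cocaine in.

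**3. Set the list beside the rationale and the definition.**

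| Drug | Introduction (local trends) | Measures |
|---|---|---|
| Marijuana | cited | listed twice |
| Alcohol | cited | listed |
| Heroin | 6.8%, above state average | only within opioids; separate item not stated |
| Cocaine | 6.2%, above state average | not listed |

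The Background definition covers illicit drugs without exception, so cocaine is within the scope of aim 1.

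**4. Scale.** Inputs: N = 720 (Quantitative Data Collection); p = 0.062 for cocaine and 0.068 for heroin (local trends section). Expected users = N × p; 95% half-width under simple random sampling = 1.96 × √(p(1 − p)/N).

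- Cocaine: 720 × 0.062 = 44.6, about 45 youths; 1.96 × √(0.062 × 0.938/720) = 0.0176, about 1.8 points.
- Heroin: 720 × 0.068 = 49.0, about 49 youths; 1.96 × √(0.068 × 0.932/720) = 0.0184, about 1.8 points.

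These figures only show that the numbers would not be trivial if the local rates applied. The half-widths ignore venue-based, purposive and snowball recruitment. The local rates are given without a recall window, whereas the survey asks about both the past 30 days and lifetime.

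**5. Undercount in overall prevalence.** Let f be the share of cocaine users who use none of the six listed substances. The shortfall in prevalence of any substance use is p × f. The documents give no information on f, so the shortfall cannot be calculated. The list includes alcohol, marijuana, tobacco and vaping, so f is probably small, but that is a judgement and not a result.

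**The case against.** The strongest reply is that this is a condensed article and the fielded questionnaire may be fuller. Item wording is commonly left to the instrument, so the absence of a printed split between heroin and other opioids is not in itself an error. That stands. A reader might infer that heroin prevalence cannot be reported at all, but the text does not support this: heroin falls within a listed category, and nothing says that opioids is one undivided item. The reply does not rescue cocaine, because the article does name the drugs and leaves cocaine out.

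A second reply is that aim 1 promises neither drug-by-drug estimates nor an estimate for illicit drugs alone. That also stands. A reader might take 0 to 6.2 percentage points as the understatement of any illicit use, running from full overlap with listed drugs to none. The protocol defines no such outcome, so that range does not describe a stated endpoint. Nor do the documents show that the loss falls most heavily on youth disconnected from school. They say such youth may use more, not that they use cocaine alone, and heavier users may well be caught through other listed drugs.

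Third, the local rates may not carry over. The Results section places other figures from the same source in the first ward only, although the Introduction words them as city-wide. The cocaine and heroin rates could be limited in the same way. This weakens the arithmetic for scale but not the mismatch.

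Finally, it is tempting to read the second marijuana entry as a slip for cocaine. The documents do not show what it stood for, or whether it stood for anything.

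**Conclusion.** The point holds for cocaine. The printed list repeats marijuana and omits a drug that falls within the protocol's own definition and forms part of its rationale. Followed as written, the survey yields no cocaine estimate, and aim 1 misses youth whose only use is cocaine. The size of that miss cannot be derived from the documents. For use of any substance it is probably small; for cocaine itself the loss is complete.

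For heroin the conclusion is narrower: the text leaves open whether it can be separated from other opioids and compared with the cited 6.8%.

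This rests on reading the list as complete, as its wording indicates, and on no fuller item list overriding it. The sampling plan, the neighbourhood measures and the modelling approach are unaffected. It is still more than a typographical slip in background text, because it sits in the definition of what will be measured.

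**What to change.** Before fielding, under Tobacco, Drug, and Alcohol Use:

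- delete the repeated marijuana entry, or name the substance it was meant to be;
- add a cocaine item with the same past-30-day and lifetime windows;
- report heroin separately from other opioids, or state that the opioid items already allow this;
- check the final list against the definition in the Background and the drugs cited in the local trends section, so that all three agree.

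If cocaine is left out on purpose, the article should say so and restrict the prevalence aim to the drugs listed.

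The cost is one to three more items in a 15- to 20-minute survey, with no extra participants. The Results section describes the study as still in planning with recruitment yet to begin, so no collected data would be affected.
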